### Outcomes

For evaluating the effectiveness of intervention, the primary outcomes include differences between intervention and control groups in the changes after one academic year intervention (9 months after the baseline) of three indexes: (a) BMI (calculated as the individual’s body weight in kilograms divided by the square of body height in meters), (b) controlled attenuation parameters (CAP, detected by FibroScan HANDY, Echosens, Paris, France), and (c) liver stiffness measurement (LSM, detected by FibroScan HANDY, Echosens, Paris, France). Secondary outcomes include differences of other measures between intervention and control groups in the changes after one academic year intervention: (a) changes in BMI Z score (SD score will be calculated based on the WHO criteria [24]), (b) changes in blood glucose, (c) changes in blood lipids (including triacylglycerol (TG), total cholesterol (TC), low-density lipoprotein cholesterol (LDL-c), and high-density lipoprotein cholesterol (HDL-c)), (d) changes in fasting insulin, (e) changes in body fat percentage, (f) changes in waist circumference, (g) changes in cardiorespiratory endurance test, (h) changes in alanine transaminase (ALT), and (i) changes in eating behaviour, physical activity behaviour, psychological status, sleep quality, etc. After the intervention finished, we will investigate anthropometric measures and fatty liver indexes in 24 and 36 months after baseline to evaluate the long-term effects of the intervention.

### Sample size

The primary outcome measures in our study included change in BMI, change in CAP, and changes in LSM. According to previous studies, the difference between the two groups in the change of BMI (effect size) was assumed to be 0.87 kg/m^2^ [15], with a standard deviation (SD) of 0.9 kg/m^2^; meanwhile, the changes in CAP and LSM were assumed to be 72 dB/m (with an SD of 75 dB/m) and 0.30 kPa (with an SD of 0.31 kPa) [25], respectively. The intracluster correlation coefficient (ICC) was 0.05, and the rate of attribution was 10% in our study. We aimed to recruit 300 students in total from 6 schools with an average of 50 students in each school. This sample size will provide power of 89.1%, 87.6%, and 88.0% with *α* = 0.05 to detect the set effect size of the change in BMI, CAP, and LSM. All power calculations were carried out in PASS 15.0.5 using the cluster-randomized function.

### Statistical analyses plan

Statistical analyses will be performed using IBM SPSS 26.0 (IBM Inc) and R 4.3.1 (R Core Team), and all two-sided *P* values of 0.05 will be considered significant. The baseline characteristics at the participant level (including anthropometric measures, blood indexes, liver ultrasound measures, and questionnaire survey indexes) and school level (school size, etc.) will be described by intervention and control arms, with normally distributed continuous data described by the mean (standard deviation) and skewed distributed continuous data described by the median (quantiles).

The intention-to-treat analysis will be applied in the analysis of the outcome for all follow-up stages. Generalized linear mixed models will be used to compare the primary and secondary outcomes at 3 and 9 months after the baseline assessment to investigate the effectiveness. Important factors associated with obesity will be adjusted, including baseline outcome values and sex. Outcomes are either binary or continuous, in that either log or linear regression functions will be used, and transformations will be done for any skewed distributed data.

In addition, subgroup analysis (e.g., sex, maternal education level, baseline BMI status), sensitivity analysis (e.g., defined overweight/obesity using the Chinese reference in main analyses and the WHO reference, before and after imputation missing data), and interactive analysis (e.g., whether the intervention effects varied by subgroup) will be explored.

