**Methods:**

This is a cluster-randomized controlled trial that conducted in children with overweight/obesity in Ningbo city, Zhejiang Province, China. Students in Grade 3 (8–10 years old) were recruited from six primary schools, with three be randomized to intervention group and three to usual practice group. The intervention program will last for one academic year and consists of health education, dietary guidance, and physical activity reinforcement. This program is characterized by encouraging four stakeholders, including School, Clinic, famIly, and studENT (SCIENT), to participate in controlling childhood obesity, assisted by m-Health technology. Assessments will be conducted at baseline and 3 months, 9 months, 24 months, and 36 months after baseline. The primary outcome will be the differences between the two groups in students’ body mass index and fatty liver index at the end of the intervention (9 months after baseline). During the implementation process, quality control methods will be adopted.

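### The mixed-model analysis is not tied to the 4 school-level degrees of freedom that the stated power appears to assume; ordinary large-sample tests would comply with the text but reject about 10–15% of true nulls at the planned ICC

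*Protocol article*

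**What the plan says.** The Abstract (Methods) describes six primary schools, "with three be randomized to intervention group and three to usual practice group". The Sample size section adds "We aimed to recruit 300 students in total from 6 schools with an average of 50 students in each school", an ICC of 0.05 and a 10% loss rate (printed as another word, read here as attrition). The BMI difference "was assumed to be 0.87 kg/m^2", "with a standard deviation (SD) of 0.9 kg/m^2". The CAP changes "were assumed to be 72 dB/m (with an SD of 75 dB/m"; LSM is given as 0.30 kPa with SD 0.31 kPa. The resulting powers are 89.1% (BMI), 87.6% (CAP) and 88.0% (LSM). On method the section says only "All power calculations were carried out in PASS 15.0.5 using the cluster-randomized function", without naming the test or its degrees of freedom.

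The Statistical analyses plan states "Generalized linear mixed models will be used to compare the primary and secondary outcomes at 3 and 9 months after the baseline assessment", adjusts for sex and the baseline value of the outcome, covers both binary and continuous outcomes, and says that two-sided *P* "values of 0.05 will be considered significant". It gives no estimation method, reference distribution or denominator degrees of freedom.

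**The concern.** Schools are the randomised units, and there are six. However many pupils each school contributes, the between-school variance relevant to the arm contrast is estimated from 6 − 2 = 4 degrees of freedom. Mixed-model software can judge that contrast in several ways. Wald z, residual df and likelihood-ratio tests are accurate with many clusters but not with six. Kenward-Roger or Satterthwaite df are meant for few clusters.

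The section fixes the model class and the threshold but leaves this choice open. Two analysts could both follow it, one running a test with about 5% error and the other a test with two to three times that. All three primary outcomes and every secondary outcome are affected in the same way, and so are the confidence intervals. A large-sample test would also not be the kind of test that the stated power appears to rest on.

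**Working it through.** **1. Which test fits the stated power?**

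Inputs from Sample size: 3 schools per arm, m = 50 × 0.9 = 45 analysed per school (135 per arm), ICC 0.05, two-sided alpha 0.05.

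- Design effect: 1 + (45 − 1) × 0.05 = 3.2.
- Standard error of the difference in SD units: √(2 × 3.2 / 135) = 0.2177.
- Standardised effects: BMI 0.87/0.9 = 0.967; CAP 72/75 = 0.960; LSM 0.30/0.31 = 0.968.
- Non-centrality (effect / 0.2177): 4.44, 4.41, 4.44.

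| Test | BMI | CAP | LSM |
|---|---|---|---|
| Stated in the protocol | 89.1% | 87.6% | 88.0% |
| t, 4 df, equal schools | 90.5% | 90.2% | 90.6% |
| t, 4 df, school-size CV 0.65 (assumed) | 88.0% | 87.6% | 88.0% |
| Normal approximation, equal schools | 99.3% | 99.3% | 99.4% |

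A t test on 268 participant-level df also gives about 99.3%. To bring a z-based calculation down to the stated powers, the ICC would have to be about 0.12 rather than 0.05. The CV of 0.65 is not in the protocol. It only shows that moderate variation in school size can account for the gap of 1.4 to 2.6 points between equal-school 4-df power and the stated values.

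**2. What happens if the mixed model is read with large-sample tests?**

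Simulation under the null: 3 v 3 schools, 45 per school, equal sizes, random intercept for school with its variance held at or above zero, no covariates, nominal two-sided 5%, 200,000 to 400,000 trials.

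| Analysis at ICC 0.05 | Type I error |
|---|---|
| REML, Wald z | 10.5–10.7% |
| REML, residual df | 10.4–10.6% |
| ML, likelihood-ratio test | 11.3% |
| ML, Wald z | 15.2–15.4% |
| REML, Satterthwaite-type df | 5.2–5.4% |
| t test on school means, 4 df | 4.9–5.0% |
| REML statistic read against the 4-df critical value | 3.5% |

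As an analytic check, a statistic that truly follows t on 4 df exceeds 1.96 in absolute value with probability 12.2%. The REML figure is a little lower because the school variance is sometimes estimated as zero, which pools the two error terms.

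**3. How far does this depend on the ICC?**

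REML with Wald z gives 3.7% at ICC 0, about 6.5% at 0.01, about 8.1% at 0.02, about 10.6% at 0.05 and about 11.6% at 0.10.

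**4. Effect on intervals.** The 4-df multiplier is 2.776 against 1.96. For the same standard error the interval is 2.776/1.96 = 1.42 times as wide.

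**The case against.** The strongest objection is that the protocol is silent here, not wrong. A reader might infer that the trial will be analysed without small-sample inference; the text does not say so. A mixed model with Kenward-Roger or Satterthwaite df fits the section as written, and a condensed article may leave the df method to an analysis plan that is not shown. That stands against any claim that an invalid test has been chosen. It does not remove the point: with six clusters the df method decides whether the test holds its level, and the article fixes the model and threshold in a form that an invalid test would satisfy.

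A reader might also take it as established that the trial was powered on a 4-df t test. That is back-calculation. The protocol names only the software function, and equal schools do not reproduce all three figures closely. BMI has a marginally smaller standardised effect than LSM but a higher stated power, so the three values do not come from one identical set of inputs. What stands is that a 4-df test lies close to the stated values and a large-sample test does not.

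Nor do the documents support reading the analysis as ignoring school. School is the only cluster they define, an ICC enters the power calculation, and a mixed model is named.

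Finally, the inflation is conditional. It needs a large-sample test and a non-trivial ICC for the outcome in question, and the simulation omits the planned covariates. It cannot be asserted that every interval will be too narrow.

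**Conclusion.** The point holds in conditional form. The analysis section does not tie inference to the 4 school-level degrees of freedom that the stated power appears to assume. If ordinary Wald z or residual-df tests were used, the type I error at the plan's own ICC of 0.05 would be about 10–11% with REML, roughly double the nominal level, and about 15% with ML and Wald z. At ICC 0.01 the REML Wald z figure is about 6.5%, and at ICC 0 there is no inflation.

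These sizes assume equal schools of 45, a continuous outcome and no covariate adjustment. The link to the power calculation is an inference from the stated figures.

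**What to change.** Add to the Statistical analyses plan, or confirm that the full analysis plan already contains:

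- **Continuous outcomes:** a linear mixed model with a random intercept for school, fitted by REML, with Kenward-Roger or Satterthwaite degrees of freedom. The alternative is a two-stage t test on school means adjusted for baseline value and sex, with 4 df. Name one of these in advance, as they are not identical in small samples.
- **Binary outcomes:** a school-level t test with 4 df, or a between-within df correction in the generalized model.
- **Confidence intervals:** the same df as the corresponding test.

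This takes a few sentences and no extra schools or pupils. The downside is wider intervals than a large-sample analysis would report. The stated power already appears to assume about 4 df, so it should need little or no revision; that is best confirmed from the original power-calculation output, including the test and the school-size variation entered.

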### Health economic evaluation

Health economics evaluation will be conducted by cost-effectiveness analysis, and a societal perspective will be used to examine whether the intervention is economically feasible. Intervention costs will cover the time for all the intervention activities spent by project staff, school staff, and all material expenses. Regarding the time spent implementing the intervention, only that spent by the project staff will be included. Time costs will be based on personal employment compensation (if available) or local average compensation for similar types of employees. Material expenses will be based on the actual purchase prices. An incremental cost-effectiveness ratio will be calculated, and a sensitivity analysis will be used to vary key parameters to check the robustness of the health economics results.

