### Intervention

The SCIENT study was based on socioecological model theory [17] and comprised activities aimed at helping children build healthy dietary behaviours and increasing physical activities in school and at home. This lifestyle intervention program focused on four components. School-based lifestyle interventions will receive support from clinics (specialist doctors and nutritionists) and family members, followed by uniform implementation manuals. All school staff will receive reimbursement to make up for their extra work during the intervention. Parental involvement is an important feature in this study. A trained professional nutritionist is allocated to each student and his/her parents to help with individualized dietary instruction, and an official account and chat group on WeChat are used as the platform for knowledge information dissemination.

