### Component 1: Carry out health education courses and distribute health education materials

Ten health education courses that were specially designed for primary school students will be released biweekly by trained class teachers, with six courses arranged in the first semester and four in the second semester. The core messages (2–2-1 core messages: 2 not: not eating excessively, not drinking sugar-sweetened beverages; 2 less: less high-energy food, less sedentary time; 1 more: more physical activities) of the courses come from our previous DECIDE-Children study [18], which mainly include the benefits of healthy weight, measurements and assessments of weight, and methods of achieving a healthy weight.

We will organize two health education activities for parents. The two health education activities with key messages similar to health education courses for students will be delivered at the beginning of each semester, and each activity will last for approximately 50 - 60 min. During the first activity, the baseline physical examination report will be fed back to parents, and an online WeChat group with approximately 30 caregivers will be established with one nutritionist for further Q&A. For the second activities, project staff will provide feedback about the student’s weight management status and answer parents’ questions about students’ weight management face-to-face.

The materials of a healthy lifestyle for weight management education will be distributed in various ways. Posters that contain weight management information released in ten courses will be put up in the classroom in intervention schools during the program. Health education books designed for elementary school students and “nutrition evaluation turnplate for Chinese primary and middle school students” [18] will be delivered to students in the intervention group. Moreover, mental health books designed for school-age students will also be distributed. Popular science articles and cartoon videos and cases with good performance will irregularly be released on our official WeChat account to intensify the consciousness of a healthy lifestyle of the students and primary caregivers.

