### Component 2: Nutrition guidance by professional nutritionists

Students will receive individual dietary guidance from an assigned professional nutritionist when they eat at home or eat school lunch and afternoon tea at school. Professional nutritionists will help caregivers to improve the dietary pattern at home. A 21-day lifestyle intensive nutrition intervention at the beginning of the first semester and a 7-day lifestyle intensive nutrition intervention at the beginning of the second semester will be provided by nutritionists through our official WeChat account. Then, the nutritionists will provide nutrition guidance at least once a week during each semester. Caregivers upload the food pictures that the participating children eat on the scheduled days, and nutritionists will give individualized advice about how to improve diet at home, taking into account their own diet characteristics. The initial goal of dietary approaches includes increasing the intake of vegetables and fruit, reducing foods with high energy density but poor nutrients, avoiding sugar-sweetened beverages, eating breakfast, appropriate portion size, and reducing eating outside [19].

Moreover, nutritionists will also help canteen staff modify school lunch and afternoon tea when children eat at school. For students in the intervention groups, healthy lunches will be prepared by dedicated canteen staff. In addition to reducing total energy, some unhealthy foods will be replaced with foods better for weight loss, for example, replacing refined rice with roughage rice, reducing foods high in oil and fat and increasing the proportion of vegetables and fruits, and replacing sweetened yogurt with sugar-free yogurt.

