### Component 3: Reinforce physical activity

Different physical activities in/outside school will be encouraged to improve the intensity and duration of physical activity in both school and home settings. According to the Chinese national requirement for “One-Hour Physical Activity on Schoolyard Every School Day”, schools will ensure that all students have at least 1 h of moderate-to-vigorous intensity activity during school hours. In addition, for participants in our program, a full-time PE teacher helped organize at least 30 min of exercise after class on school days three times a week, mainly focusing on moderate- to high-intensity aerobic exercise supplemented by anaerobic exercise. Any other form of exercise with family members and partners outside school will also be encouraged.

Each student in the intervention schools will receive an Amazfit Neo sports watch (Zepp Health, Beijing, China), which can record exercise, heart rate, sleep conditions, etc. Caregivers can check the student’s exercise and sleep conditions through an App linked with the watch, which will be helpful for improving the physical activity level of students at home.

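### The economic evaluation defines its staff-time costs in two incompatible ways under a societal label; if the narrower rule is applied, incremental cost is understated

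*Protocol article*

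**What the plan says.** The Health economic evaluation section makes three statements about scope, one after another.

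- Perspective: "a societal perspective will be used to examine whether the intervention is economically feasible".
- Costs: "Intervention costs will cover the time for all the intervention activities spent by project staff, school staff, and all material expenses".
- Time: "Regarding the time spent implementing the intervention, only that spent by the project staff will be included".

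It then values time at personal compensation where available, or otherwise at a local average for similar employees. Materials are valued at actual purchase prices. The result is described as follows: "An incremental cost-effectiveness ratio will be calculated, and a sensitivity analysis will be used to vary key parameters". The parameters to be varied are not named.

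Other sections show who does the work. Under Component 1, ten courses "will be released biweekly by trained class teachers, with six courses arranged in the first semester and four in the second semester". Under Component 2, "healthy lunches will be prepared by dedicated canteen staff". Under Component 3, "a full-time PE teacher helped organize at least 30 min of exercise after class on school days three times a week". Component 4 adds teacher training of about 50 to 60 minutes at the start of each semester. The Intervention section states: "All school staff will receive reimbursement to make up for their extra work during the intervention". Caregivers are asked to upload food pictures on scheduled days (Component 2), and two parent activities of about 50 to 60 minutes each are planned (Component 1). According to the Control group section, control schools receive none of the components.

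**The concern.** An analyst following this section cannot tell whether school-staff delivery time belongs in the numerator of the ratio. One sentence puts it in and the next takes it out. The choice matters because school staff carry much of the delivery, and because the trial treats their extra work as a real cost by paying for it.

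The restrictive sentence also does not fit the declared perspective. In its ordinary meaning, a societal perspective counts resources whoever bears them. A rule that admits only project-staff time is the scope of a programme provider. A ratio calculated that way but labelled societal would be read by education or health authorities as covering costs that it leaves out.

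**Working it through.** The article gives no cost, ratio or threshold, so there is no figure to reproduce. The check is textual, with a short illustration.

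**1. Can the two sentences be read together?** One attempt is to separate intervention activities (second statement) from implementing the intervention (third statement), so that, for example, teacher training is counted and delivery is not. The article does not draw that line. Even if it did, course teaching, extra exercise sessions and lunch preparation would be left out. Another possibility is that the third statement is garbled and was meant only to exclude project-staff time spent on research. The text does not say so. No other section settles the question.

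**2. Is the excluded time recovered elsewhere?** The reimbursement in the Intervention section is not obviously a material expense, since materials are valued at purchase prices, and the economic section does not say that it enters the costs. The sensitivity analysis does not clearly help either: varying an included parameter does not bring in an excluded cost category.

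**3. Direction if the restrictive sentence governs.** The ratio is R = ΔC / ΔE, incremental cost over incremental effect. If a share s of the true ΔC is omitted and ΔE is unchanged, then

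reported R = (1 − s) × ΔC / ΔE = (1 − s) × true R.

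For assumed shares s = 0.10, 0.25 and 0.50, the reported ratio is 0.90, 0.75 and 0.50 of the true one. These shares only show how the ratio responds. The article supports no particular value.

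**4. Illustration of hours, not costs.**

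- After-class exercise, one teacher per session assumed: 3 sessions × 0.5 h = 1.5 h a week per school. The number of teaching weeks is not given; 28 to 38 is assumed.
  - 28 weeks: 1.5 × 28 = 42 h per school, × 3 schools = 126 h
  - 32 weeks: 1.5 × 32 = 48 h per school, × 3 schools = 144 h
  - 38 weeks: 1.5 × 38 = 57 h per school, × 3 schools = 171 h
- Teacher training: 2 × 50/60 to 2 × 60/60 = about 1.7 to 2.0 h for each teacher who attends both sessions.
- Parent activities: the Sample size section plans 300 students in 6 schools, so about 150 families in the intervention arm. With one caregiver per family at both activities (assumed), 150 × 2 × 50/60 = 250 h, up to 150 × 2 × 60/60 = 300 h.

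Time spent on picture uploads is not estimated, because neither the number of scheduled days nor the minutes per upload is given.

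**The case against.** The strongest reply is that the second statement does include school staff, so the evaluation may turn out properly costed on that count. This stands. A reader might infer from the third statement that the ratio is biased, or that school-staff work is costed at zero. The article does not establish either, because it does not say which sentence governs or whether the reimbursement enters the costs.

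It also stands that not every school-staff hour is incremental. Control schools keep their usual teaching plan and presumably serve lunch. A health lesson that replaces another lesson, or a modified lunch that replaces an ordinary one, is not wholly an added cost. The after-class exercise sessions are the clearest extra time.

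Caregiver time is the weaker part. A one-paragraph summary may omit items that a fuller economic plan lists. It belongs here only because the restrictive sentence, by its wording, admits no time but that of project staff, under a perspective named as societal.

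Finally, the economic evaluation is in neither the stated aims nor the primary or secondary outcomes, so its reach is limited. None of this removes the contradiction. It is a rule stated twice in incompatible forms, not a detail left to another document.

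**Conclusion.** The cost scope is contradictory and should be reconciled. The consequence is conditional. If the restrictive sentence is applied, reimbursed extra school-staff work and caregiver time are left out, incremental cost is understated, and with a positive effect the ratio looks more favourable than a societal ratio would. If the broader sentence is applied, school-staff time is counted, but caregiver time is still not listed.

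The size cannot be derived from the article. The hours above rest on an assumed number of teaching weeks and assumed attendance, and they are not converted to money. A reader might go further and infer that the conclusion on economic feasibility would be wrong. That does not follow: no cost, effect or threshold is given, and an understated cost need not reverse a conclusion. The efficacy analyses are not affected.

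**What to change.** Reconcile the two sentences before any cost-effectiveness ratio is reported, in one of two ways.

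1. Keep the societal perspective. Remove the restriction to project staff. Cost the incremental time of school staff from reimbursement records, the delivery schedule and the compensation rule already stated. Count only time beyond what the school would have spent anyway. Estimate caregiver time from the planned contacts and vary it in the sensitivity analysis.
2. Keep the narrow scope. Name it as a programme-provider perspective and drop the word societal.

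The first route costs some extra tallying and will probably give a less favourable ratio. It has to rely on records and schedules: the end-of-intervention questionnaire fell around June 2023 and the article appeared in March 2024, so new items could no longer be added to it. The second route is a change of wording only, at the price of a narrower claim.
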